#### Cost-effectiveness analyses

All cost-effectiveness analyses will use the intention-to-treat principle. Quality-adjusted life-years (QALYs) will be calculated from the results of the SF-12 based on an algorithm developed by Brazier et al. [99] For the Veteran perspective, we will compare Veterans' incremental out-of-pocket costs (e.g., transportation, over-the-counter medications, and co-payments) to their incremental QALY impacts. For the VHA perspective, incremental direct intervention costs will be compared to ongoing direct medical utilization costs. This cost-benefit analysis will address whether, economically, yoga should be a treatment option for the VA population. For the society perspective, we will conduct a cost-utility analysis by comparing the incremental societal costs for each treatment arm (i.e., direct medical, nonmedical, and productivity costs) to the incremental change in QALYs [100]. We will use bootstrap methods to calculate confidence intervals [101] and perform one-way sensitivity analyses to determine the robustness of our estimates with different assumptions used to value productivity [102]. Combined non-back pain and back pain-related utilization will be used for all of these analyses. We will also perform sensitivity analyses using only back pain-related utilization.

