Secondary outcomes					
Pain medication use		✓	✓	✓	✓
PTSD CheckList—Civilian version (PCL-C)		✓	✓	✓	✓
Health-related quality of life (SF-12)		✓	✓	✓	✓
Satisfaction with treatment		✓	✓	✓	✓
Global improvement			✓	✓	✓
Cost-effectiveness outcomes					
Work productivity		✓	✓	✓	✓
Medical utilization and cost		✓	✓	✓	✓
Exploratory outcomes					
PROMIS-29 and pain interference		✓	✓	✓	✓
Depression (PHQ-9) and anxiety (GAD-7)		✓	✓	✓	✓
Relationship satisfaction (DAS)		✓		✓	✓
Pain self-efficacy (PSEQ)		✓		✓	✓
Sleep quality (PSQI)		✓		✓	✓
Coping strategies (CSQ)		✓		✓	✓
Post-concussive symptoms (NSI)		✓		✓	✓
Possible covariates and confounders					
Exercise history		✓	✓	✓	✓
Low back pain treatments		✓	✓	✓	✓
Alcohol, drugs, and smoking		✓		✓	✓

*Sociodemographic information includes gender, age, relationship status, ethnicity, race, income, housing, education level, and military service history

DVPRS = Defense and Veterans Pain Rating Scale; RMDQ = Roland Morris Disability Questionnaire; PROMIS = Patient Reported Outcome Measurement Information System; SF-12 = Short Form 12-item Health Survey; PHQ-9 = 9-item Patient Health Questionnaire; GAD-7 = 7-item General Anxiety Disorder survey; DAS = Dyadic Adjustment Scale; PSQI = Pittsburgh Sleep Quality Index; NSI = Neurobehavioral Symptom Inventory

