### Data analysis

We will conduct both intention-to-treat and per-protocol analyses, with the intention-to-treat analysis being primary. Descriptive statistics including means, medians, and standard deviations for continuous variables, and the number and proportions for categorical variables will be reported. All analyses will be performed at the α = 0.05 level of significance.

The success of randomization will first be assessed. We will compare the two groups on baseline characteristics and demographics, including stratification variables, with Student’s t test or chi-square test, as appropriate, using an α = 0.1 level of significance. Variables that differ between the groups at baseline will be considered possible confounders and adjusted for in subsequent analyses.

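### The only adjustment rule reaching the QALY comparison is a baseline test at α = 0.1; baseline SF-12 utility should be a prespecified covariate and the QALY contrast defined

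*Protocol article*

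**What the plan says.** Under Cost-effectiveness analyses the article states that "Quality-adjusted life-years (QALYs) will be calculated from the results of the SF-12" by a published algorithm. The Veteran perspective sets out-of-pocket costs against "to their incremental QALY impacts". The society perspective sets total costs against "to the incremental change in QALYs"; what change means there is not explained. For uncertainty: "We will use bootstrap methods to calculate confidence intervals". The sensitivity analyses named concern the valuation of productivity and the restriction to back-related utilization. No regression model or baseline term is given for QALYs.

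The opening of Data analysis, which precedes all the analysis subsections, compares the arms at baseline "using an α = 0.1 level of significance" and then says: "Variables that differ between the groups at baseline will be considered possible confounders and adjusted for in subsequent analyses". It does not say whether SF-12 utility is among the variables tested.

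Table 3 schedules the SF-12 at baseline and at 6, 12 and 24 weeks, so a baseline utility will exist for each Veteran. Randomization is stratified by age, PCL-C score and partnered status, none of which balances utility directly.

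**The concern.** A QALY total over 24 weeks includes the utility at baseline, and baseline utility also predicts the later values. If the arms differ at baseline by chance, part of that difference appears as a QALY difference. A significance test is a poor way to decide whether to correct for it. The test picks up only large imbalances, whereas the benefit of adjustment comes from the correlation between baseline and outcome, which is there whether or not the test is significant.

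Over so short a horizon the QALY difference will be small, so an ordinary imbalance can be similar in size to a plausible effect. At stake are the Veteran and society results of a named secondary aim.

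**Working it through.** **Inputs from the document.** 120 Veterans randomized 1:1 (60 per arm); 20 % dropout (48 per arm); threshold α = 0.1; SF-12 at weeks 0, 6, 12 and 24. The article gives no figure for QALYs. Its stated powers of 97 %, 82 % and 80 % reproduce with 48 per arm (24 for the PCL-C subset) using the noncentral t: 97.2 %, 82.9 % and 80.7 %. They concern other outcomes and are not affected.

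**Assumptions not in the document.** Utility SD 0.08–0.15; equal correlation ρ of 0.5–0.7 between visits; QALY as trapezoid area under the curve.

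**1. What the test lets through.** Largest unflagged difference = t(0.95; 118 df) × √(2/60) = 1.658 × 0.1826 = 0.30 SD (0.34 SD with 48 per arm). The mean unflagged absolute difference is 0.12 SD, and about 17 % of trials would have an unflagged difference above 0.2 SD.

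**2. Gain against an unadjusted area.** The trapezoid weights are (3, 6, 9, 6)/52 years. Their numerators have sum 24 and sum of squares 162. In units of SD²/52²:

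- variance of the total: V = 162(1−ρ) + 576ρ
- covariance with baseline: C = 3 + 21ρ
- residual variance after adjustment: V − C²

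| ρ | V | C | V − C² | ratio to V | SE reduction |
|---|---|---|---|---|---|
| 0.5 | 369.0 | 13.5 | 186.75 | 0.51 | 29 % |
| 0.6 | 410.4 | 15.6 | 167.04 | 0.41 | 36 % |
| 0.7 | 451.8 | 17.7 | 138.51 | 0.31 | 45 % |

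**3. Gain against change from baseline.** Subtracting baseline utility over the whole period gives weights (−21, 6, 9, 6)/52, with sum 0 and sum of squares 594. The variance is 594(1−ρ) = 297.0, 237.6 and 178.2. The adjusted variances are those of step 2, so the ratios are 0.63, 0.70 and 0.78 and the SE falls by 21 %, 16 % and 12 %.

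**4. Shift from a difference at the threshold.** Unadjusted area: (C/52) × 0.303 × SD. This runs from 0.260 × 0.303 × 0.08 = 0.0063 to 0.340 × 0.303 × 0.15 = 0.0155 QALY, or 1.2–1.4 standard errors of the unadjusted estimate. For scale, an assumed utility gain of 0.03 at each visit after baseline is worth 0.03 × 21/52 = 0.012 QALY. With change from baseline the multiplier is 21(ρ−1)/52, that is −0.20 at ρ = 0.5 and −0.12 at ρ = 0.7, so the same imbalance acts in the opposite direction.

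**5. What the stated rule recovers.** This was checked in 20,000 simulated null trials per ρ, with utility among the tested variables and t-type inference. Variance relative to unadjusted was 0.79, 0.75 and 0.71 under the α = 0.1 rule, against 0.51, 0.41 and 0.31 with adjustment in every trial. The SE under adjustment in every trial is therefore lower than under the rule by 1 − √(0.51/0.79) ≈ 20 % at ρ = 0.5 and 1 − √(0.31/0.71) ≈ 34 % at ρ = 0.7. The rule's type I error was 3.2 %, 2.7 % and 2.1 % at a nominal 5 %, so it is conservative and costs power.

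**The case against.** The strongest reply is that the article does not fix a QALY model. A reader might infer that QALYs will be computed with baseline utility left out. The text does not say so. It is silent, a condensed article may leave covariates to an analysis plan that is not shown, and the reference to change in the society contrast may already bring baseline in. That stands, and the point therefore rests on the adjustment rule that is stated.

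Nor is the α = 0.1 test the only handling of baseline in the article. Primary outcome analyses puts baseline in the longitudinal model. Secondary back pain outcome analyses treats the SF-12 summary scores in the same way and adjusts medication use for its baseline value without any test. This also stands. None of it is extended to QALYs, however, and the rule at the start of Data analysis, although it forbids no other covariate, is the only one whose scope covers them.

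A reader might also infer bias. Under randomization the unadjusted comparison is unbiased over repeated trials, and bootstrap intervals reflect chance imbalance as sampling variation. What remains is wider intervals and error conditional on the imbalance that occurs. Most of the shift in step 4 comes through the assumed correlation; the baseline visit itself carries only 3/24 of the area.

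Reading change as change from baseline does not remove the issue. It reverses the direction of the carried-over imbalance and leaves a gain of 12–21 %.

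**Conclusion.** The point holds as one of precision and prespecification. The only stated rule reaching the QALY comparison depends on a baseline significance test that passes differences up to about 0.30 SD with 60 per arm, and the contrast itself is undefined. Always adjusting cuts the SE by 29–45 % if the alternative is an unadjusted area, and by 12–21 % if it is change from baseline. If utility is among the tested variables, the gain over the stated rule with an unadjusted area is about 20–34 %.

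These percentages rest on equal between-visit correlations of 0.5–0.7 and a trapezoid over 24 weeks; the absolute QALY shifts also rest on the assumed SD. The documents do not support a claim that baseline utility is excluded, that the result is systematically biased, or that all three perspectives are affected: the VHA comparison sets costs against costs.

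**What to change.** State in the analysis plan how the QALY total is formed from the four SF-12 visits and what the incremental contrast is. Then estimate incremental QALYs at 12 and 24 weeks by regressing each Veteran's total on arm and baseline SF-12 utility, refitted in every bootstrap replicate and independent of any baseline significance test. With baseline utility in the model, total area and change from baseline give the same arm coefficient, so the ambiguity no longer affects the estimate.

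Adjusting incremental costs for baseline cost would be an optional parallel step; no size has been worked out for it here.

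The cost is a sentence or two of text. Baseline SF-12 is already scheduled, and neither data collection nor sample size changes.

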### Study interventions

The study interventions start within two weeks of randomization to allow adequate time for pre-intervention qualitative interviews. All interventions, related supplies, and transportation to study visits are provided at no cost to participants. Veterans in both treatment arms can continue to see their providers and receive routine care including medication.

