Yoga classes contain no more than eight to ten Veterans and two yoga teachers to assure a low Veteran-to-instructor ratio (no more than five Veterans to one teacher). This arrangement maximizes effectiveness and safety, and allows flexibility in yoga teacher scheduling based on the study’s needs. Veterans are asked to attend one 75-minute class per week and receive reminder phone calls the day before each scheduled class. Attendance is taken by research staff. We provide $10 travel compensation for each yoga session. Mats and props are provided. Each class includes a yoga breathing exercise (*pranayama*), discussion of yoga philosophical principles, yoga postures (*asanas*), and a relaxation exercise (*svasana*). Veterans are frequently advised to proceed carefully and slowly. The difficulty of postures increases throughout the 12 weeks (Table 2). The 12-week intervention period is divided into four 3-week segments, titled Opening to Something New, Listening to Your Back, Engaging Your Power, and Bringing it Home. Posture variations, modifications, and various aids (e.g., block, chair, strap, wall) are built into the protocol to accommodate a range of abilities. Yoga participants are encouraged to practice at home for 30 minutes on days when they do not have class. To help Veterans practice at home, they receive a guidebook describing and depicting the protocol (see Additional file 1), yoga mat, strap, two blocks, and home practice instructional videos (see Additional file 2-5). Home practice videos portray Veterans in an introductory video describing the value of yoga practice in their own lives, two 30-minute videos that follow the same structure as group yoga classes, and one 20-minute extended breathing and relaxation video. Veterans are given a link to view the home practice videos online or, if requested, they receive a take-home DVD.

**Table 2 Tab2:** Twelve-week standardized hatha yoga protocol

Yoga posture (*asana)* or class component	Classes incorporating component by segment			
	Segment 1	Segment 2	Segment 3	Segment 4
	Weeks 1–3	Weeks 4–6	Weeks 7–9	Weeks 10–12
	Opening to Something New	Listening to Your Back	Engaging Your Power	Bringing it Home
Breathing exercise	✓	✓	✓	✓
Knees to chest pose^*^	✓	✓	✓	✓
Knees together twist pose	✓	✓	✓	✓
Pelvic tilt pose^*^	✓			
Big toe pose^*^		✓	✓	✓
Cat and cow pose*	✓		✓	
Wheel pose^*^	✓		✓	
Chair pose^*^	✓	✓	✓	
Shoulder openers^*^	✓	✓	✓	✓
Crescent moon pose^*^	✓	✓		✓
Mountain pose^*^	✓	✓	✓	✓

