#### Cost-effectiveness

We use a multi-method approach to collect cost data at baseline, 6 weeks, 12 weeks, and 24 weeks. Since our interventions may influence other common comorbidities of cLBP (e.g., depression [52]), we measure both back-related utilization and total medical utilization. Direct medical costs are measured and consist of the cost of (1) implementing the interventions themselves and (2) ongoing medical utilization before, during, and after the intervention. Intervention implementation costs (e.g., non-study-specific staff hours, materials, facility use) are captured from study records and valued at their actual costs. Ongoing total VA medical utilization including visits, hospitalizations, tests, radiology, and medications are taken directly from the electronic medical record system. Direct medical costs are valued at their actual costs to the VA. Any non-VA medical utilization (e.g., chiropractors, out-of-pocket back-related expenses) is obtained from a cost questionnaire completed by the Veteran with the primary initial recall period being the past 6 weeks and is valued at the reported actual price paid by Veterans. Indirect costs (i.e., lost productivity) for employed Veterans will be calculated as the number of lost productive hours (as reported in the Work Productivity and Activity Impairment questionnaire) multiplied by a national average cost of employment for each Veteran’s general job category. Lost productivity costs for those not in the work force are assumed to be captured by their report of overall quality of life [96]. Lost productivity costs for those looking for work will be considered in the sensitivity analyses.

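### Trial-paid class travel can make yoga look too cheap from the Veteran's perspective, and a 6-week recall used at week 24 would leave weeks 12–18 of self-reported costs unobserved in both arms

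*Protocol article*

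**What the plan says.** All references are to the protocol article. Cost-effectiveness at 12 and 24 weeks, from the Veteran, VHA and societal perspectives, is a secondary aim (Specific aims).

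**Travel**
- The Veteran analysis compares "incremental out-of-pocket costs (e.g., transportation, over-the-counter medications, and co-payments) to their incremental QALY impacts" (Cost-effectiveness analyses).
- The societal analysis uses "incremental societal costs for each treatment arm (i.e., direct medical, nonmedical, and productivity costs" (same section).
- Study interventions states: "All interventions, related supplies, and transportation to study visits are provided at no cost to participants".
- Hatha yoga adds: "We provide $10 travel compensation for each yoga session". There is one class a week for 12 weeks.
- The Education section describes a book, mailed newsletters and telephone check-ins, with no classes to travel to.
- Intervention costs come from study records at actual cost. The examples given are staff hours, materials and facility use (Cost-effectiveness).

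**Recall**
- "We use a multi-method approach to collect cost data at baseline, 6 weeks, 12 weeks, and 24 weeks" (Cost-effectiveness).
- Non-VA use, including out-of-pocket back-related expenses, comes from a Veteran questionnaire "with the primary initial recall period being the past 6 weeks", and is "valued at the reported actual price paid by Veterans".
- VA use needs no recall: "Ongoing total VA medical utilization including visits, hospitalizations, tests, radiology, and medications are taken directly from the electronic medical record system".

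The planned sensitivity analyses concern the valuation of productivity and a restriction to back-related utilization. None concerns travel or the recall interval.

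**The concern.** **Travel.** The Veteran analysis sets out to measure a cost that the trial itself partly or wholly removes, and for class travel it does so in one arm only. An out-of-pocket figure collected under those conditions describes the trial's subsidy, not what a Veteran would pay for weekly yoga in ordinary care. The article presents the work as informing whether yoga is cost-effective and scalable, so the cost outside the trial is the one that matters.

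**Recall.** The survey interval doubles after week 12, from 6 weeks to 12, while the only recall period stated stays at 6. If that period applies at week 24, part of the self-reported cost is never collected, although VA costs and QALYs cover the full horizon. This is a data-collection choice: an analysis plan can impute the missing weeks but cannot recover them.

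At stake are the Veteran result at both horizons (travel), and the Veteran and societal results at 24 weeks (recall). The co-primary outcomes are not involved.

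**Working it through.** The article gives no cost-effectiveness figure to reproduce, so the check is direct arithmetic on its stated schedule and payments.

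**1. Size of the travel payments**

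Inputs: $10 per class and 12 weekly classes (Hatha yoga); adherence threshold of 9 classes (Primary outcome analyses); 120 participants randomized 1:1, hence 60 in the yoga arm (Study design).

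Formula: payment = $10 × classes attended.
- Full attendance: 10 × 12 = $120 per participant.
- At the adherence threshold: 10 × 9 = $90 per participant.
- Whole yoga arm at full attendance: 60 × 120 = $7,200.
- Education arm: no classes, so $0.

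These are the payments, not an estimate of real travel cost, which the article does not give. If Veterans report travel net of the payment, and a trip costs at least $10, the Veteran cost of yoga is understated by these amounts. If a trip costs less than $10, the understatement is the trip cost itself. Any class transport supplied in kind would add to it. Transport to survey visits would not, because both arms attend those in person.

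**2. Weeks covered by a 6-week recall**

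Inputs: post-baseline cost surveys at weeks 6, 12 and 24; recall of 6 weeks. Each survey at week *s* covers weeks *s* − 6 to *s*.

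| Survey | Weeks covered |
|---|---|
| 6 | 0–6 |
| 12 | 6–12 |
| 24 | 18–24 |

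- Intervention period: 12 of 12 weeks covered.
- Follow-up period: 6 of 12 covered; weeks 12–18 missed (50%).
- 24-week horizon: 18 of 24 covered; 6/24 = 25% missed.

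With recall back to the last survey (12 weeks at week 24), coverage becomes 24 of 24.

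**3. Direction of the recall gap**

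The same questionnaire schedule applies to both arms. Let *y* and *e* be weekly self-reported costs in yoga and education during follow-up, assumed constant. The true increment is 12(*y* − *e*). The captured increment, if costs are simply summed, is 6(*y* − *e*). The weekly costs below are assumptions chosen to show the sign, not data.

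| *y*, *e* ($/week) | True increment | Captured |
|---|---|---|
| 10, 10 | 0 | 0 |
| 8, 12 | −48 | −24 |
| 12, 8 | +48 | +24 |

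The follow-up difference is halved toward zero. Yoga's relative cost is understated if yoga participants spend more in those weeks, overstated if they spend less, and unchanged if spending is equal.

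**The case against.** Several objections carry weight.

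- **The recall gap does not favour yoga.** A reader might infer that the missed weeks also understate yoga's cost. The documents do not support that: the gap removes cost from both arms, and the sign depends on spending that nobody yet knows. This objection stands in full.
- **The gap is conditional.** The recall period is described as both primary and initial, which may mean another period applies later. The questionnaire is not shown, and a journal article may leave visit-specific wording or scaling rules to fuller documents. This stands as a limit on certainty. The article nevertheless fixes one recall period and a schedule that it does not fit.
- **The price-paid rule is stated for non-VA medical use.** No sentence applies it to class travel, so it cannot be said that travel will be recorded as zero. This stands. The point rests instead on transportation being named as an out-of-pocket cost while the trial covers it.
- **The intervention-cost list is only illustrative.** Study records could include the $10 payments, and the societal analysis has a nonmedical component. It is tempting to say that the societal cost of yoga is understated too, but that follows only if the payments are left out. Counting them there would still not correct the Veteran perspective.
- **Transport to study visits is offered to participants generally.** Only class travel is specific to the yoga arm, so not all of the transport support can be assigned to yoga. This stands.
- **Changing the recall mid-trial mixes recall periods.** This is true, and it is a cost of the remedy.

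**Conclusion.** Two limited points hold, both within a secondary aim.

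**Travel, Veteran perspective.** Out-of-pocket costs net of the trial's travel support would understate what yoga costs a Veteran outside the trial. The cash payments are up to $120 per yoga participant at 12 classes and $90 at 9, with nothing comparable in the education arm. This assumes that reported costs are net of the payments. The societal analysis is affected only if study records omit them. How far any cost-per-QALY result would move cannot be stated, since the article gives no incremental cost or QALY figures.

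**Recall, 24-week Veteran and societal analyses.** If the 6-week recall is used at week 24 and the costs are not scaled, self-reported non-VA and out-of-pocket costs for weeks 12–18 are missing in both arms: half of follow-up and a quarter of the horizon. The bias has no fixed direction; at constant weekly rates any follow-up difference is halved. The 12-week analysis is fully covered, and VA utilization is unaffected because it comes from the record.

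**What to change.** **Travel.** In the Veteran analysis, value travel to each attended yoga class at its real-world cost (distance or fare × recorded attendance), regardless of who pays. In the societal analysis, count that travel once: if study records already hold the $10 payments, replace them rather than adding to them. Report the as-paid version as a sensitivity analysis. This needs one unit-cost assumption, and class attendance is already recorded. The consequence is that yoga will look less favourable from the Veteran's perspective.

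**Recall.** State the recall period for each survey, and set the week-24 period to the interval since the last completed survey (12 weeks if the week-12 survey was done). For participants already surveyed at week 24 with a 6-week recall, scale the recalled cost to the interval and test that assumption in a sensitivity analysis. The article reports that the trial is still recruiting, so the change can reach later participants. It is a small change to the questionnaire wording. The costs are less accurate recall over the longer period and, for a change made mid-trial, a mixture of recall periods that must be recorded and handled in the analysis.

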**Methods/design:**

This study is a parallel randomized controlled trial comparing yoga to education for 120 Veterans with chronic low back pain. Participants are Veterans ≥18 years old with low back pain present on at least half the days in the past six months and a self-reported average pain intensity in the previous week of ≥4 on a 0–10 scale. The 24-week study has an initial 12-week intervention period, where participants are randomized equally into (1) a standardized weekly group yoga class with home practice or (2) education delivered with a self-care book. Primary outcome measures are change at 12 weeks in low back pain intensity measured by the Defense and Veterans Pain Rating Scale (0–10) and back-related function using the 23-point Roland Morris Disability Questionnaire. In the subsequent 12-week follow-up period, yoga participants are encouraged to continue home yoga practice and education participants continue following recommendations from the book. Qualitative interviews with Veterans in the yoga group and their partners explore the impact of chronic low back pain and yoga on family relationships. We also assess cost-effectiveness from three perspectives: the Veteran, the Veterans Health Administration, and society using electronic medical records, self-reported cost data, and study records.

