### Specific aims

This study will determine if yoga can become a safe, clinically effective, cost-effective, and scalable nonpharmacologic approach to address the physical and psychosocial dimensions of cLBP in Veterans [67]. This study is a 24-week two-arm randomized controlled trial for 120 Veterans with cLBP with four specific aims:Primary aim – to determine the effectiveness of a structured, reproducible 12-week series of hatha yoga classes, supplemented with home practice, compared to an education control group, for decreasing pain intensity and improving back-related functionSecondary aim – to evaluate the effectiveness of yoga compared to education for improving PTSS and other psychosocial outcomes, including depression, anxiety, self-efficacy, and copingSecondary aim – to evaluate the cost-effectiveness of yoga for cLBP at 12 weeks and 24 weeks from three perspectives: the Veteran, the Veterans Health Administration, and societyExploratory aim – to explore the effect of cLBP on family relationships, as well as yoga’s impact on the Veteran, family, and family functioning

The results of this study have the potential to impact the approach and management of cLBP according to the Army Surgeon General Pain Management Task Force vision, i.e., having a more integrative and interdisciplinary focus on active self-care approaches that empower Veterans to have greater control of their condition [63].

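### The VHA-perspective analysis is a cost offset with no health outcome, so on its own it cannot fully answer the VHA cost-effectiveness aim

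*Protocol article*

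**What the plan says.** The economic aim under Specific aims is "to evaluate the cost-effectiveness of yoga for cLBP at 12 weeks and 24 weeks from three perspectives: the Veteran, the Veterans Health Administration", with society as the third. The abstract repeats it: "We also assess cost-effectiveness from three perspectives: the Veteran, the Veterans Health Administration, and society".

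The section Cost-effectiveness analyses then defines one analysis per perspective:

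- **Veteran:** incremental out-of-pocket costs are related "to their incremental QALY impacts".
- **VHA:** "For the VHA perspective, incremental direct intervention costs will be compared to ongoing direct medical utilization costs".
- **Society:** incremental direct medical, nonmedical and productivity costs are related "to the incremental change in QALYs".

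The VHA comparison is given a name and a purpose: "This cost-benefit analysis will address whether, economically, yoga should be a treatment option for the VA population". The same section gives the source of the health measure, "Quality-adjusted life-years (QALYs) will be calculated from the results of the SF-12", and plans bootstrap confidence intervals. The Cost-effectiveness section under Data collection says that VA utilization comes from the electronic record and is valued at actual VA cost. Table 3 schedules the SF-12 at baseline and at 6, 12 and 24 weeks.

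**The concern.** A cost-effectiveness result relates a difference in cost to a difference in health. A cost-benefit analysis values the health difference in money. The VHA comparison does neither. It sets what the intervention costs against what is spent on care, which tells the payer about net spending only.

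The mismatch matters because the protocol attaches the payer's question to this comparison. If yoga raises net VHA spending, which is a plausible result for a staffed class programme followed for 24 weeks, the planned result is a net cost with nothing beside it to judge whether the cost is worthwhile. If yoga lowers spending, the comparison alone does not show that health was at least maintained. In both cases the health information has to come from outside the VHA analysis.

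**Working it through.** The protocol gives no cost, utility difference or willingness-to-pay threshold, so there is no figure to reproduce. The check is first of structure.

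| Perspective | Promised in the aim | Cost side | Health side |
|---|---|---|---|
| Veteran | cost-effectiveness | out-of-pocket | QALYs |
| VHA | cost-effectiveness | intervention and medical utilization | none |
| Society | cost-effectiveness | medical, nonmedical, productivity | QALYs |

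Write ΔI for the difference in intervention cost (yoga minus education), ΔU for the difference in VA utilization cost, and ΔQ for the difference in QALYs.

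- What the planned VHA comparison can yield: net cost = ΔI + ΔU.
- What the aim needs: (ΔI + ΔU) / ΔQ or, with a threshold λ, net benefit = λ × ΔQ − (ΔI + ΔU).

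The first quantity is only one ingredient of the second. The sentence on the VHA also attaches the word incremental to intervention cost alone and calls utilization ongoing. That ΔU is a difference between arms is therefore a sensible reading, but it is not stated.

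An illustration shows how far the missing term matters. **All inputs are assumed; none comes from the documents.** Take net VHA costs of $200 (for example ΔI = $600 and ΔU = −$400) and of $300 per Veteran. For health, take a utility gain of 0.03 held over 24 weeks, ΔQ = 0.03 × 24/52 = 0.0138, then half of that, 0.0069, as if the benefit built up gradually, and then none. Ratios use the unrounded ΔQ.

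| ΔQ | Net cost $200 | Net cost $300 |
|---|---|---|
| 0.0138 | about $14,400 per QALY | about $21,700 per QALY |
| 0.0069 | about $28,900 per QALY | about $43,300 per QALY |
| 0 or below | yoga dominated | yoga dominated |

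Within each column the planned comparison reports the same dollar amount in every row, while the implication for a payer changes.

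The society ratio does not fill the gap, because its numerator includes nonmedical and productivity costs that the VHA does not bear. The Veteran ratio counts only out-of-pocket costs. No other section gives a VHA cost per QALY.

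**The case against.** The strongest reply is that the design is deliberate. The Discussion says that group self-care such as yoga, provided that it works, could save the VHA money and be cost-effective for society. On that reading the VHA question is cost saving, effectiveness is tested elsewhere in the trial, and cost-effectiveness in the aim is an umbrella term for three kinds of economic analysis. Much of this stands. Cost saving is a legitimate payer question, and the planned comparison answers it. If yoga saves money and the clinical results are no worse, the two together support offering it.

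What remains is that the aim and abstract name cost-effectiveness for the VHA, the analysis section calls the comparison cost-benefit although no benefit is valued, and the case in which yoga adds net cost is left without an answer. These are things that the article states, not details that it leaves to a fuller document.

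Two stronger readings are tempting. A reader might infer that the plan would reject yoga for the VHA unless it pays for itself. The protocol states no accept or reject rule, and it limits the question to the economic side. A reader might also infer that the VHA perspective is missing altogether. It is not: a VHA economic result is planned, in a form narrower than the aim.

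**Conclusion.** The point holds as a mismatch between aim, label and analysis. The VHA comparison is a cost-offset analysis. It shows whether yoga pays for itself, but on its own it cannot fully address the treatment-option question, because a net cost cannot be judged without the health gained. That a wrong adoption decision would follow is not supported.

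The conclusion follows from the wording of the protocol and needs no numerical assumption. Its size in dollars per QALY is unknown, and the figures above only illustrate how the answer depends on the omitted term. The matter affects one of three perspectives in a secondary aim. It does not touch the co-primary outcomes, their analysis or the sample size. It should be corrected before the economic analysis is run.

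**What to change.** 1. Keep the comparison of intervention and utilization cost, with both stated as differences between arms. Call it a cost-offset or budget result and drop the cost-benefit label.
2. Add for the VHA perspective the incremental net VHA cost (intervention plus all VA utilization, yoga minus education) per incremental SF-12 QALY, at 12 and at 24 weeks, with the bootstrap intervals already planned.
3. Base the statement on whether yoga makes economic sense for the VA on both results.

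The cost is a few lines of text, one more analysis and one more table. No new data are needed, since the SF-12 and VA costs are already being collected. The SF-12 data will not be complete for everyone: the Sample size section assumes 20 % dropout, so on that assumption about 120 × 0.80 = 96 Veterans would have full follow-up, and the missing QALYs will need handling as in the other two perspectives.
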